##### Promoting trans-sectional care—the SOFIA handbook

Owing to the Danish organization of health care and social care into different sectors resorting under separate laws, formal trans-sectional care plans are not feasible. However, each general practitioner assigned to the intervention arm will receive a specialized handbook, specific for their municipality and regional affiliation, containing contact information of relevant social or health care actors, and helplines in case of substance abuse and an increased risk of suicide and self-harm.

##### MMQ part 1

Apart from improving physical health, the SOFIA study aims to improve the quality of life among the participants. To measure the quality of life, we use the patient-related outcome measure, MMQ. MMQ was developed for patients with multimorbidity, including SMI. In the SOFIA pilot trial, we want to examine if the simultaneous use of MMQ as a conversation tool and an outcome assessment will bias the MMQ as an outcome measure. Therefore, the general practices will be cluster-randomized in two subgroups, with 2 general practices from each region in both subgroups. All patients are asked to complete the MMQ part 1 (MMQ1) before the prolonged consultation. In the first subgroup, the relative sum-scores of six scales will be provided to the general practitioners via an electronic link. During the educational course, the general practitioners in the first subgroup are instructed on how to use the six scales’ sum-scores as a clinical conversation aid during the “patient part” of the consultation. In the other subgroup, the general practitioners will not have access to the MMQ1 scores.

#### Control group

Primary care patients in the control group will receive usual care during the study period. In the control group, the general practitioners will not have access to the MMQ1 six scales’ sum scores. Usual care includes free access to primary healthcare both during and out of office hours. Of relevance in this context is that in Denmark all primary care patients suffering from chronic conditions, i.e., diabetes, cardiovascular diseases, COPD and asthma, rheumatoid arthritis, osteoporosis, thyroid conditions, and all mental conditions, are offered an annual disorder-specific health-check, and medication and treatment review by their general practitioner.

#### End-of study

The study period ends on September 30, 2021. All patients in the intervention and control groups receive the same questionnaires as at baseline (MMQ, EQ-5D-5L) to be returned to the research team by mail or through RedCap. This concludes the study period for all participating patients.

### Concomitant care

Any new interventions or initiatives introduced by local health authorities, municipalities, researchers, health organizations, and the like, aimed at improving healthcare for persons with psychiatric conditions, will be recorded during the study.

### Outcomes measures

The overall aim of the pilot trial is to assess the feasibility and quality of trial management, intervention content, and implementation. To qualify the content of the intervention and its implementation, a formative process evaluation of the pilot trial will be conducted with a twofold purpose: to assess the implementation platform and to inform the definitive SOFIA trials’ preliminary program theory [29]. The formative aspect of the evaluation will ensure more rapid feedback which can give rise to iterative changes during the pilot trial after which the results of these adjustments can be assessed. This formative approach will maximize the potential for an optimum model before the definitive trial [29]. The study design is a mixed-method study using data from an electronic data registration system (REDCap, see below), registers, and qualitative methods (interviews and observations). For the objectives, where threshold criteria are given, these will be used to decide if, and in that case, how to progress to the large-scale RCT. Not reaching these thresholds does not necessarily indicate unfeasibility but will be an incentive to re-evaluate and possibly adjust the design and/or elements of the intervention.

#### Primary outcome measures

To assess the implementability of the intervention

Concerning the implementation, we will assess the implementation platform for the intervention by assessing fidelity (if and to what extent the intervention was performed as planned and the educational recommendations were followed) and barriers and facilitators for implementation concerning, e.g., comprehensibility, acceptability by practices, preparation, and the integration of the intervention into existing practices. This will be done by performing qualitative semi-structured interviews with general practitioners and staff in the intervention group during the pilot trial and observations of the introductory course and prolonged consultations.
2.To assess the feasibility of the design in terms of recruitment of practices and patients and assess retention of patients during the intervention

The feasibility of the recruitment of practices and patients will be assessed using the proportion of contacted general practices, which agree to participate in the study and the eligibility and consent rate of patients. We consider a participation rate of at least 20% of the contacted general practices and at least 60% of the contacted patients as an indication that our recruitment strategy is feasible. Based on registrations by the practices in REDCap, feedback and questions regarding support from practices during the process, and interviews with general practitioners and staff after the recruitment process, we will assess the appropriateness of the recruitment process and the introduction and support to the participating practices.

Retention of patients will be assessed as the proportion of recruited patients in the intervention group who attend the first consultation, and the minimum threshold for attendance is set at 90%. Information on measures such as non-return of consent forms, non-shows by participating patients in general practice, and difficulties reaching patients will be collected. Based on interviews with the practices, we will explore their work related to ensuring patient attendance.
3.To assess the feasibility of collection of outcome measures and thereby obtain preliminary data to inform the required sample size in the definitive trial

All patients, regardless of allocation, will complete the two outcome questionnaires the MMQ and the EQ-5D-5L questionnaire at baseline, after randomization, and at the end of the pilot trial. Based on the number of returned questionnaires, we will calculate response rates and the proportion of missing data in each completed questionnaire. We set a minimum acceptable threshold for the response rate before randomization of both questionnaires at >90% with a maximum proportion of missing data at <10%. We set a minimally acceptable response rate at >90% for both questionnaires at the end of the study period in both the intervention and the control group.

Data on mortality and in- and outpatient admissions during the study period in the participating patients will be collected from the national patient registries after completion of the pilot trial. These data, along with the scores of the MMQ, and the EQ-5D-5L questionnaires, will be used to estimate the necessary sample size to power the definitive trial, which primary endpoints are mortality and quality of life, as measured by the MMQ.

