**Methods:**

The SOFIA pilot trial is designed as a cluster randomized controlled trial targeting general practices in two regions in Denmark. We aim to include 12 practices, each of which is instructed to recruit up to 15 community-dwelling patients aged 18 and older with SMI. Practices will be randomized by a computer in a ratio of 2:1 to deliver a coordinated care program or usual care during a 6-month study period. A randomized algorithm is used to perform randomization. The coordinated care program includes educational training of general practitioners and their clinical staff educational training of general practitioners and their clinical staff, which covers clinical and diagnostic management and focus on patient-centered care of this patient group, after which general practitioners will provide a prolonged consultation focusing on individual needs and preferences of the patient with SMI and a follow-up plan if indicated. The outcomes will be parameters of the feasibility of the intervention and trial methods and will be assessed quantitatively and qualitatively. Assessments of the outcome parameters will be administered at baseline, throughout, and at end of the study period.

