To assess the implementability of the intervention including the fidelity and acceptability of the intervention for patients and general practitionersTo assess the feasibility of the design in terms of recruitment of practices and patients and to assess retention of patients and practices during the interventionTo assess the feasibility of collection of outcome measures and thereby obtain preliminary data to inform the required sample size in a definitive, large-scale efficacy trial—hereafter referred to as ”The SOFIA Trial”

The secondary objectives of the study are:
To examine whether our recruitment strategy is at risk for preferential inclusion of patients with a favorable prognosisTo examine to which extent general practitioners’ use of patients’ response to the MultiMorbidity Questionnaire (MMQ) (see section “Data collection before randomization” for a description of the MMQ below), measuring quality of life in patients with multimorbidity, during the prolonged consultations threatens the validity of the questionnaire as an outcome measureTo assess and inform selected aspects of the program theory relating to the prolonged consultations and the educational course

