### Power analysis and sample size

As this is a pilot trial, a formal sample size calculation is not performed. We aim to include 12 practices, each recruiting up to 15 patients per practice, amounting up to 180 patients in total. We considered this number sufficiently informative on the practicalities of delivering the intervention and collecting outcome data.

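### The pilot's own deaths, from at most about 90 person-years, are too few to supply the mortality rate for sizing the definitive trial

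*Protocol article*

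**What the plan says.** The third primary objective, listed at the end of Background and rationale, is to test whether outcome measures can be collected and thereby to "obtain preliminary data to inform the required sample size in a definitive, large-scale efficacy trial". Item 3 of Primary outcome measures says how. It takes "Data on mortality and in- and outpatient admissions during the study period in the participating patients" from the national registries once the pilot is complete. These data, together with the MMQ and EQ-5D-5L scores, "will be used to estimate the necessary sample size to power the definitive trial, which primary endpoints are mortality and quality of life", the latter measured by the MMQ. The population (participants), the window (the study period) and the use are therefore all fixed.

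The size of the pilot is set under Power analysis and sample size: "We aim to include 12 practices, each recruiting up to 15 patients per practice, amounting up to 180 patients in total". There, "a formal sample size calculation is not performed", and the number is justified by what it can show about practicalities, not about event rates. The abstract says that practices will "deliver a coordinated care program or usual care during a 6-month study period". The protocol gives no expected number of deaths, no mortality rate, no precision target and no other named source for the rate.

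**The concern.** A trial with mortality as a primary endpoint needs a control-group death rate. For a given relative effect, the number of patients required is roughly inversely proportional to that rate. A cluster trial also needs some idea of how the rate varies between practices. The plan looks to the pilot's participants for this input, yet a group this small, observed for half a year, will produce a handful of deaths or none.

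The Harms section already accepts that the sample is too small for an analysis of harms. The same sample is nevertheless expected to inform the power of a mortality trial. At stake is one of the two main inputs to a stated primary objective: a calculation that relied on the pilot's death count could be wrong by an order of magnitude.

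**Working it through.** **Inputs from the protocol.** 12 practices, up to 15 patients each, 6-month study period.

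**Inputs assumed.** Annual mortality of 1-3%, with 0.5-5% as a wider range. The protocol gives only life years lost, not a rate.

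**Step 1: the plan's own figure.** 12 × 15 = 180, which agrees with "amounting up to 180 patients in total". Maximum follow-up is 180 × 0.5 = 90 person-years.

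**Step 2: expected deaths.** Expected deaths = 90 × rate. The Poisson chance of none is exp(−expected).

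| Assumed annual mortality | Expected deaths | Chance of none |
|---|---|---|
| 0.5% | 0.45 | 64% |
| 1% | 0.9 | 41% |
| 2% | 1.8 | 17% |
| 3% | 2.7 | 7% |
| 5% | 4.5 | 1% |

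Even at 3%, the chance of five deaths or fewer is exp(−2.7) × Σ 2.7^k/k! for k = 0 to 5, which is 0.0672 × 14.04 = 0.94.

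**Step 3: precision for each count d.** The exact Poisson 95% limits are χ²(0.025; 2d)/2 and χ²(0.975; 2d+2)/2, each divided by 90 person-years. This step does not use the assumed rate.

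| Deaths seen | Rate per 100 person-years | 95% limits | Upper ÷ lower |
|---|---|---|---|
| 0 | 0 | 0 to 4.1 | not defined |
| 1 | 1.1 | 0.03 to 6.2 | 220 |
| 2 | 2.2 | 0.27 to 8.0 | 30 |
| 3 | 3.3 | 0.69 to 9.7 | 14 |
| 5 | 5.6 | 1.8 to 13.0 | 7 |

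**Step 4: effect on the definitive trial.** This is an illustration only. It assumes a hazard ratio of 0.75, two-sided 5% significance, 80% power, 1:1 allocation, one year of follow-up and no design effect. Schoenfeld's formula gives 4 × (1.960 + 0.842)² / (ln 0.75)² ≈ 380 deaths. The number of patients is 380 divided by the mean one-year death probability in the two arms.

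- Two deaths in the pilot: about 19,700 patients, with the interval limits giving about 5,600 to 162,000.
- Three deaths in the pilot: about 13,200 patients, with limits of about 4,700 to 63,000.

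**Step 5: sensitivity to the window.** If the study period also covered the 5-month enrolment phase in Table 2, follow-up would be 180 × 11/12 = 165 person-years, and 1-3% would give 1.7 to 5.0 expected deaths. For a given count, the ratio of upper to lower limit stays the same. Recruitment below 180 would lower the expected count.

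**Step 6: between-practice variation.** With five deaths or fewer, at least 12 − 5 = 7 of the 12 practices would have none. Such counts cannot support an estimate of how mortality varies between practices.

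**The case against.** The strongest reply is that this is a feasibility pilot and that the objective speaks only of preliminary data. The sample size statement lists several data sources and nowhere says that external mortality rates will be ignored. No pilot participant, allocation, progression threshold or pilot analysis depends on it, and the MMQ data needed for the other primary endpoint remain usable. Most of this stands, and it limits how serious the point is. It does not remove the point: the protocol commits these deaths to the sample size, names no other source for the rate, and makes informing that sample size a primary objective.

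A reader might go further in four ways that the document does not support.

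- **That the pilot will see one to three deaths.** This rests on an assumed rate, and on that same assumption no deaths at all is a real possibility.
- **That the pilot's rate is biased low.** End-of-life patients and those judged to function too poorly are excluded, and the protocol itself raises selective recruitment. If the definitive trial keeps the same criteria and consent process, however, the participants' rate is the relevant one. Selective recruitment is already a secondary objective, to be examined through registries, and the Discussion promises to revisit the strategy if needed.
- **That the MMQ input fails as well, because 12 practices estimate an intracluster correlation poorly.** The protocol states no such correlation and no plan to take one from the pilot.
- **That the definitive trial will be mis-sized.** That would follow only if the pilot's count were used without other evidence.

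**Conclusion.** The point holds for the mortality input only. Follow-up of at most 90 person-years cannot give a death rate precise enough to size a trial. The 95% limits differ about 220-fold with one death, 30-fold with two and 7-fold with five, and with none there is no usable point estimate. The expected 0.9 to 2.7 deaths, and the 41% to 7% chance of none, depend on the assumed 1-3% per year. The imprecision at any count from 0 to about 5 does not.

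This is worth correcting before the definitive trial is planned. It is not a flaw in the pilot's conduct or in its feasibility conclusions, and the MMQ and EQ-5D-5L scores and response rates remain reasonable inputs.

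**What to change.** Amend item 3 of Primary outcome measures along these lines:

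- **Source of the rate.** Take the mortality rate, and its variation between practices, from national registry data over several years on the wider eligible population with severe mental illness. Use the closest registry equivalents of the inclusion criteria, and apply those exclusions that can be coded.
- **Sensitivity range.** Show how the required number changes with the code mapping and with selective participation. The protocol defines diagnoses by ICPC-2 codes held at the practice and says that the ICD-10 codes correspond only roughly. Two exclusions, an incorrect or outdated diagnosis and functioning as judged by the general practitioner, cannot be coded.
- **Role of the pilot's deaths.** Limit them to showing that registry linkage and collection work. Do not use them for a rate, or for a mortality ratio between participants and non-participants, which would rest on the same few events.
- **What stays.** Keep the pilot's MMQ and EQ-5D-5L scores and response rates as inputs.

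The cost is a wider extract from registries that the trial already plans to use, plus the change of wording. No extra patients are needed. The drawback is that the registry population only approximates the trial's, hence the sensitivity range. Estimating between-practice variation also assumes that the extract can link patients to practices, which the protocol does not address for non-participants.

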#### Secondary outcome measures

To examine whether our recruitment strategy is at risk for preferential inclusion of patients with a favorable prognosis

To assess if, and to what extent, selective recruitment is present in our study, we aim to use national patient registries and registrations in REDCap to examine potential differences in demographic, socio-economic, and health-related characteristics between eligible patients who agreed and who declined participation in our study.
2.To examine to which extent use of the quality of life questionnaire (MMQ1) during the prolonged consultations threatens the validity of the questionnaire as an outcome measure

It is the intention, in the definitive trial, that the general practitioners can use the MMQ1 as a conversation tool to help them identify issues that should be addressed during the consultation. In this scenario, in the intervention arm, the general practitioners have access to the aggregated patients’ MMQ scores, and patients might have a different understanding of the questions after having discussed them during the consultation as opposed to the participants in the control group. This might compromise the validity of the MMQ1 as a primary outcome in the definitive trial. Within the pilot study, we aim to empirically test for this risk of bias. To this end, in randomly selected 50% of the intervention practices, the general practitioner will have access to the aggregated score of selected domains in the MMQ1. In the remaining 50% of the intervention practices, MMQ1 scores will be concealed for the general practitioner. This sub-study is designed as a small equivalence trial nested in the pilot study. The aim is to show that the two approaches are not different in terms of mean change in MMQ1 scores before and after the intervention by using the scores of MMQ2 and EQ-5D-5L as anchors.
3.To assess and inform selected aspects of program theory relating to the prolonged consultations and the educational course

Concerning the program theory, we will assess selected proposed connections, mechanisms, and contextual conditions influencing intervention implementation and outcomes, mainly to gain a preliminary indication of the effectiveness of the prolonged consultations (change in diagnosis, medication, referrals, increased contact) and the effectiveness of the educational course in changing the clinical practice approach. This can give rise to elaborations of the program theory and adjustments of the intervention before the definitive trial. These issues will be assessed by a combination of the registrations in REDCap, observations, and interviews with practices in the intervention group. Furthermore, we will conduct interviews in all allocation groups on usual care and in the control group on the non-study care they have received during the study period.

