#### Exclusion criteria primary care patients with SMI

Patients will be excluded from participation if they are:
A.Subjected to any type of legal measure as stipulated in the Danish Mental Health Care Act (Psykiatriloven), e.g., forced detention or medication;B.Registered with a dementia diagnosis ICPC-2 p70, roughly corresponding to ICD-10 F0.01-0.03 or registered with organic psychosyndrome or other neurological diseases (ICPC-2 P71, N73, N99)C.Receiving end-of-life careD.Non-Danish speakersE.Psychiatric diagnosis appears to be incorrect or outdatedF.Assumed by the patient’s general practitioner to have an overall functional level that is too low for meaningful participation in the trial (use of this criterion will be evaluated on an individual basis by the trial management team to minimize the risk of selective inclusion).

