#### Identification, eligibility assessment, and recruitment of patients with SMI

Participating practices will be instructed to collect the International Classification of Primary Care version 2 (ICPC-2) codes and ATC-codes from the electronic medical record on all patients who are registered at the practice at the commencement of the study and send these to the research team. ICPC-2 codes are routinely used in Danish medical practice.

A computer algorithm will randomly select a sample of 45 patients who fulfill the externally verifiable inclusion criteria for each participating general practice. This selection will be stratified, in that each sample of 45 patients includes 15 patients who meet diagnostic criteria B1, B2, or B3 respectively. The research team sends this list of 45 potentially eligible patients to the general practitioners. General practitioners are instructed to screen these lists for correct diagnoses. In case of uncertainty regarding diagnosis, general practitioners should contact the research team. When a diagnosis is verified by the general practitioner, the general practitioner will assess the eligibility of the listed patients according to the exclusion criteria described above. General practitioners are instructed to document any reasons for exclusions and any reasons for deviating from the exclusion criteria. General practitioners are instructed to recruit at least 2 patients from each diagnostic subgroup (corresponding to the inclusion criteria B1, B2, and B3). We employ a reimbursement limit of 15 patients per practice. Patients participating in the study will not receive financial compensation.

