The general practices will establish the initial contact with patients who were found eligible. Practice staff will contact potentially eligible patients via telephone, and provide brief oral information about the study. When approaching patients, practice personnel are instructed to register the date and means of contact, e.g., telephone or email, and the number of attempts. In case the patient does not respond, an email, text message, or message on voicemail is sent. If a patient cannot be reached after at least three attempts, the patient will be excluded from participation. Patients, who express interest in participating in the study, will be invited to an initial 10–30-min enrolment visit at the general practice. General practices are instructed by the research team to send an information leaflet and a copy of the informed consent form by mail or email to patients before they visit their practice. During the enrolment visit, further questions regarding the study will be discussed. If patients agree to participate, written informed consent will be obtained. Moreover, all patients receive the questionnaires MMQ and the EQ-5D-5L measuring quality of life and health status after they visited their practice. Patients can either choose to receive the questionnaire in print from their general practice or via their e-Boks (provider of secure platforms and digital post-boxes) from the research team. A more detailed description of the properties of these questionnaires is provided below in the section “Data collection before randomization”—quality of life measurements. Patients are asked by the general practitioner to complete these questionnaires online through a link in their secured email or return them by mail in a prepaid envelop to the research team.

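### Selective recruitment is checked only by comparing eligible patients who agreed with those who declined, so prognostic selection at the earlier recruitment steps could go undetected

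*Protocol article*

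**What the plan says.** Under *Secondary outcome measures*, item 1, the protocol article states the aim: "To examine whether our recruitment strategy is at risk for preferential inclusion of patients with a favorable prognosis". The stated means is to use registries and REDCap entries to "examine potential differences in demographic, socio-economic, and health-related characteristics between eligible patients who agreed and who declined participation in our study". No other comparison of characteristics is given for this objective.

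The route to agreeing or declining is described under *Identification, eligibility assessment, and recruitment of patients with SMI* and in the patient exclusion criteria:

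- **List.** "A computer algorithm will randomly select a sample of 45 patients who fulfill the externally verifiable inclusion criteria for each participating general practice", with 15 from each of three diagnostic groups.
- **GP screen.** The GP verifies diagnoses and applies the exclusion criteria. Two rest largely on judgement: E (diagnosis apparently wrong or out of date) and F ("an overall functional level that is too low for meaningful participation in the trial").
- **Cap.** "We employ a reimbursement limit of 15 patients per practice". At least 2 patients per diagnostic group are to be recruited. No order of contact is stated.
- **Non-contact.** "If a patient cannot be reached after at least three attempts, the patient will be excluded from participation".

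The protocol also records part of these losses. GPs document reasons for exclusion and for departing from the criteria. Reasons for non-eligibility go into REDCap. Practices log the date, means and number of contact attempts. The eligibility rate and difficulties in reaching patients are collected as feasibility data. Each use of criterion F is reviewed by the trial management team in order to limit selective inclusion.

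**The concern.** The objective concerns the whole recruitment strategy, but the comparison covers only its last step. A patient enters it only after passing the GP screen, being chosen for contact and being reached. If prognosis influences any of those steps, both comparison groups are shifted in the same direction and the contrast between them need not show it.

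This matters because the Discussion says that the recruitment strategy will be re-evaluated if selective recruitment is found. The bias named there is recruitment of patients already willing to seek medical attention. Patients who cannot be reached are a plausible opposite of that group, and they have neither agreed nor declined. A falsely reassuring result would carry the same strategy into a definitive trial whose primary endpoints are mortality and quality of life.

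**Working it through.** **Inputs from the protocol article.** 12 practices, up to 15 patients each (*Power analysis and sample size*); 45 listed patients per practice, a cap of 15 and a minimum of 2 per diagnostic group (*Identification, eligibility assessment, and recruitment*); a participation threshold of "at least 60% of the contacted patients as an indication that our recruitment strategy is feasible" (*Primary outcome measures*, item 2).

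**The plan's own figure.** 12 × 15 = 180, which reproduces the stated maximum.

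**Freedom of choice within the cap.** The diagnostic minimum fixes 3 × 2 = 6 of 15 places. The other 9 have no stated rule on which eligible patients are approached.

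**Coverage of the planned comparison.** Assume full lists and a filled cap.

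- Listed: 12 × 45 = 540.
- Contacted at exactly 60% participation: 180 / 0.60 = 300, or 25 per practice.
- Declined, at most: 300 − 180 = 120.
- Compared, at most: 180 + 120 = 300 of 540 (56%).
- Outside, at least: 540 − 300 = 240 of 540 (44%), or 20 per practice.

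With the cap filled, higher participation means fewer contacts and more patients outside:

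| Participation | Contacted | Outside the comparison |
|---|---|---|
| 60% | 300 | 240 (44%) |
| 70% | about 257 | about 283 (52%) |
| 80% | 225 | 315 (58%) |
| 100% | 180 | 360 (67%), with no decliners |

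The reverse also holds. At 180 / 540 = 33% participation the whole list would have been contacted.

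**Non-contact.** Suppose, as an assumption, that 25%, 50% or 75% of the 120 contacted non-participants were not reached rather than declining. The comparison then covers 180 + 90 = 270, 180 + 60 = 240 or 180 + 30 = 210 of 540 (50%, 44%, 39%).

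**Can the comparison miss real selection?** Illustration, all assumptions: half of the 540 (270) have a poor prognosis, 300 are contacted, all contacted patients are reached, and 60% consent regardless of prognosis. Let poor-prognosis patients be half as likely to be contacted as the others.

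- Contact probability, good prognosis: 300 / (270 + 0.5 × 270) = 0.741; poor prognosis: 0.370.
- Contacted: 200 good, 100 poor.
- Agreed: 60 of 180 poor (33%). Declined: 40 of 120 poor (33%).
- Not contacted: 170 of 240 poor (71%). Whole list: 50%.

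Agreed versus declined shows no difference, although participants have 33% poor prognosis against 50% on the list. With a contact ratio of 0.75 the shares are 43% in both comparison groups, 59% among those not contacted and 50% on the list.

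**The case against.** The strongest reply is that the earlier losses are documented. Exclusion reasons, deviations, non-eligibility, contact attempts, eligibility rate and difficulties in reaching patients are all recorded, criterion F is reviewed centrally, and GPs are told to consult the team when a diagnosis is uncertain. The research team draws the lists from codes that the practices send, so it holds the sampling frame. This stands. A reader might infer that GP selection and non-contact leave no trace, and the protocol does not support that. What remains is that these records give counts and reasons, and none is tied to a comparison of characteristics. The gap is clearest for eligible patients never contacted once the cap is reached, for whom no specific record is stated.

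A reader might also infer that the 60% participation threshold is defective because unreachable patients leave its denominator. The text does not favour that. The recruitment section uses contact for the attempt and then describes what happens when a patient does not respond. Being excluded from participation means not being enrolled; it does not say that the patient is removed from the rate. At most the word could be defined.

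The 44% is open to fair criticism too. It includes properly ineligible patients (for example dementia or a wrong diagnosis), it assumes that every practice can fill a list of 45, and a practice that works through its list without reaching 15 has no never-contacted group. Nothing in the document shows that the earlier steps do in fact lose the sicker patients. The Discussion openly names selective recruitment as a limitation, and thresholds are not binding go/no-go rules.

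**Conclusion.** The point holds in a limited form. The stated comparison is confined to patients found eligible, contacted and reached, so it cannot by itself answer whether the recruitment strategy favours patients with a good prognosis. Losses before consent are partly counted and explained, but the characteristics of those lost are not compared with those of participants.

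The figure of at least 240 of 540 indicates scale only. It rests on full lists, a filled cap and exactly 60% participation, and it is not an estimate of wrongly lost patients. The prognosis illustration shows that the comparison can miss selection; it does not show that selection occurs. The change should be made before the comparison is run: a stated objective is not met by its stated analysis, and a random reference sample already exists.

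**What to change.** 1. Under *Secondary outcome measures*, item 1, compare participants with all other listed patients, split by stage: excluded by the GP (by criterion), eligible but not contacted, not reached, declined. Use the ICPC-2 and ATC codes and REDCap entries already held, and registry data as far as approvals allow for people who did not consent. Have practices mark eligible patients who were never contacted as such.
2. Send each diagnostic list in computer-generated random order and instruct practices to contact eligible patients in that order until the cap is reached. If contact has already taken place, only item 1 applies.
3. As a clarification, state that *contacted* in the 60% threshold means at least one contact attempt.

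Cost: a sort order on lists that the team already generates, one additional status code, and a wider comparison group. The real burden is extending registry linkage from decliners to all listed patients; the protocol article does not show whether approvals cover this. If they do not, the comparison can still be made on the codes and REDCap data.
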